**Discussion:**

Results from this rigorous study design should provide strong support that statins lower aldosterone levels in humans. These results may explain some of the beneficial effects of statins that are not attributed to the LDL-lowering effect of this important class of medications. Results would demonstrate that statin lipophilicity is an important attribute in lowering aldosterone levels. The outcomes of this program will have implications for the design of studies involving statin medications, as well as for the differential use of classes of statins.

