#### Randomization of study drug

Prior to Study Visit 1, participants will be randomized to simvastatin 20 mg per day, pravastatin 40 mg per day, or placebo using a block randomization schedule with block size of 3 and maintaining equal distribution of female/male sex. Double-blinding will be maintained by use of the Investigational Drug Services Pharmacy at BWH who will prepare and dispense study drug and assign randomization.

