### Chronic effect of statins on aldosterone secretion (study visits 2 & 3)

### Study visit 2

After approximately 6 weeks of daily study drug, participants will begin the same 5-day study diet run-in prior to their second inpatient study visit. They will then be admitted to the CCI for one night and repeat the baseline and angiotensin II infusion procedures described during Study Visit 1.

*Anticipated Results from Study Visit 2: After 6 weeks, statin drugs will decrease angiotensin II-stimulated aldosterone secretion relative to placebo, and simvastatin treatment will result in a larger blunting of angiotensin II-stimulated aldosterone secretion compared to pravastatin.*

Study Drug dose escalation: Blood will be drawn to assess LDL-cholesterol level after approximately 6 weeks on study drug (approximately 5 days before Study Visit 2). Following completion of Study Visit 2, the dose of study medication will be doubled (40 mg simvastatin, 80 mg pravastatin, 0 mg placebo) if the LDL-cholesterol has decreased less than 35% compared to its level at screening. If the LDL-cholesterol level has decreased more than 35% since screening, they will remain on the same dose. Participants will be unaware of LDL-cholesterol level or dose changes to ensure blinding. Participants will then continue their daily study medication for an additional 6 weeks after completion of Study Visit 2.

### Study visit 3

After approximately 12 weeks of treatment with study drug, participants will complete the same controlled diet run-in for 5 days followed by admission to the CCI for one night. They will repeat all study procedures as in Study Visit 2. After completing Study Visit 3, participants will have finished study participation and will discontinue the study medication. LDL-cholesterol values from the screening visit will then be disclosed with recommended healthcare provider follow-up if indicated.

*Anticipated Results from Study Visit 3: After 12-weeks, statin drug will decrease angiotensin II-stimulated aldosterone secretion relative to placebo, and simvastatin treatment will result in a larger blunting of angiotensin II-stimulated aldosterone secretion compared to pravastatin.*

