### Laboratory measurements

Twenty-four hour urines for sodium, potassium, aldosterone, and creatinine will be collected on each day of the inpatient visits. Sodium and potassium will be measured by flame photometry (Cole-Parmer, Vernon Hill, IL, USA). Aldosterone will be measured using an assay from Immuno-Biological Laboratories Inc., Minneapolis, MN, USA. Serum aldosterone and plasma renin activity (Immuno-Biological Laboratories Inc., Minneapolis, MN, USA) and serum cortisol (Beckman Coulter, Brea, CA, USA) will be measured from samples drawn at three time points (before infusion, after 1 ng/kg/min infusion, and after 3 ng/kg/min infusion) during inpatient Visits 1, 2, and 3, and also during the Posture Visit. A lipid panel will be taken at the lipid check visit.

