### Statistical analysis

Sample size calculations were derived from our observational report [13] that described the relationship between statin users and circulating aldosterone levels. In this study, the measured aldosterone level in response to angiotensin II infusion (3 ng/kg/min for 45 mins) within each participant group (self-reported statin users and non-statin users) was normally distributed with a mean population standard deviation of 16 ng/dL. If the true difference between an active study drug (simvastatin or pravastatin) and placebo mean aldosterone level is 14 ng/dL (based on the population means from our observational study), we will need to study 30 individuals in each of the three study arms to be able to reject the null hypothesis that the aldosterone levels across arms is equal with probability (power) 0.85. The Type 1 error probability associated with this test is 0.025, since 2 study drugs will be compared independently with placebo. Secondary endpoints will report the difference between simvastatin and pravastatin and evaluate the dose-relationship and that with LDL-cholesterol lowering effects by drug. We will aim to enroll 105 individuals and anticipate a 15% drop-out rate to enable evaluation of 90 individuals (30 per arm).

The three arms of the study population will be compared for baseline characteristics to assess quality of randomization assignment based on age, BMI, sex, race, and aldosterone levels. We anticipate that compared to placebo, the aldosterone response to angiotensin II after 12 weeks of simvastatin will be significantly muted, indicating a decrease in aldosterone secretory activity. Based on our previous report in isolated adrenal ZG cells, we anticipate that the less lipophilic statin (pravastatin) will have little ability to dampen the aldosterone response to angiotensin II infusion and will be similar to placebo.

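### The dose-relationship endpoint cannot separate dose from LDL response, because dose varies within a drug only through LDL-triggered doubling after Visit 2; the LDL endpoint needs a stated time point

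*Protocol article*

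**What the plan says.** All references are to the protocol article.

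- **Secondary endpoints (Statistical analysis).** "Secondary endpoints will report the difference between simvastatin and pravastatin and evaluate the dose-relationship and that with LDL-cholesterol lowering effects by drug". No time point or method is given for these three questions.
- **Starting dose (Randomization of study drug).** "participants will be randomized to simvastatin 20 mg per day, pravastatin 40 mg per day, or placebo using a block randomization schedule". Each drug has one starting level.
- **Dose change (Study visit 2).** After Visit 2 the dose is doubled "if the LDL-cholesterol has decreased less than 35% compared to its level at screening". Otherwise: "If the LDL-cholesterol level has decreased more than 35% since screening, they will remain on the same dose". In the placebo arm, doubling is nominal (0 mg).
- **LDL measurement (Study visit 2; Laboratory measurements).** "Blood will be drawn to assess LDL-cholesterol level after approximately 6 weeks on study drug (approximately 5 days before Study Visit 2"). The laboratory section adds: "A lipid panel will be taken at the lipid check visit". No week-12 lipid panel is named. Visit 3 is described by: "They will repeat all study procedures as in Study Visit 2".
- **Purpose of escalation (Discussion).** It is there to maximise the aldosterone-lowering effect. Estimating a dose-response is not given as a reason.
- **Conclusion foreseen (Abstract, Discussion).** "Results would demonstrate that statin lipophilicity is an important attribute in lowering aldosterone levels".

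**The concern.** A dose-relationship needs participants on different doses who are otherwise comparable. Here nobody is randomised to a dose level within a drug. The higher level goes by rule to those whose LDL responded less, a group that will include people who took fewer tablets. If LDL response and aldosterone response share a cause such as adherence or drug exposure, the doubled group will tend to have higher aldosterone at week 12 even when dose does nothing. The reported dose-relationship could then be false or point the wrong way.

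The LDL question has a related weakness. The article's rationale is that aldosterone lowering is an effect apart from LDL lowering, so the pairing of the two measurements matters. The one on-treatment LDL value named reflects the starting dose. Set against week-12 aldosterone, it would describe a dose that some participants no longer take.

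**Working it through.** **The plan's own figure.** Inputs from Statistical analysis: difference 14 ng/dL, SD 16 ng/dL, type 1 error 0.025 (taken as two-sided), power 0.85. By the normal approximation, n per arm = 2 × (2.241 + 1.036)² × 16² / 14² ≈ 28.1, so 29. The t-test needs 30, with power 0.858 at 30. The stated 30 per arm reproduces, and nothing below changes it.

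**Where dose variation comes from.**

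| Period | Dose levels within a drug | What sets the level |
|---|---|---|
| First doses to Visit 2 | one | randomised drug |
| After Visit 2 to Visit 3 | two | LDL fall below or above 35% |

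Any comparison of dose levels between participants on the same drug is therefore necessarily read at week 12. Dose is a threshold function of LDL fall, so at any given LDL fall only one dose occurs and a regression on both has no overlap to work with. A comparison confined to people close to 35% is not realistic with 30 per arm. Placebo supplies no parallel dose contrast.

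**Size of the false difference.** Suppose that the true effect of doubling is zero, and that within an arm LDL fall and week-12 aldosterone are jointly normal, with larger LDL falls going with lower aldosterone at correlation ρ in absolute value. Let p be the share doubled, z_p the standard normal quantile at p, φ the standard normal density and σ the outcome SD. Then

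mean(doubled) − mean(undoubled) = ρ σ φ(z_p) / [p(1 − p)]

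σ = 16 and 30 per arm come from the article. p and ρ are assumptions, because it gives no LDL-response figures.

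Example, p = 0.5 and ρ = 0.3: 0.3 × 16 × 0.399 / 0.25 = 7.7 ng/dL.

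| Share doubled | ρ = 0.1 | ρ = 0.3 | ρ = 0.5 | SE of the contrast |
|---|---|---|---|---|
| 0.3 | 2.6 | 7.9 | 13.2 | 6.4 |
| 0.5 | 2.6 | 7.7 | 12.8 | 5.8 |
| 0.7 | 2.6 | 7.9 | 13.2 | 6.4 |
| 0.9 | 3.1 | 9.4 | 15.6 | 9.7 |

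SE = 16 × √[1/(30p) + 1/(30(1 − p))]; at p = 0.5 this is 16 × √(1/15 + 1/15) = 5.8.

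**Is 30-70% doubled a reasonable range?** The share is Φ((35 − mean fall)/SD of fall). For an assumed SD of 10 or 15 percentage points, a mean fall of 40% gives 0.31 or 0.37, 30% gives 0.69 or 0.63, and 25% gives 0.84 or 0.75. The share can therefore differ between the two drugs if their LDL effects differ.

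**Sensitivity to the SD.** In the article 16 ng/dL is the SD of aldosterone levels within groups of an observational study. If the component that moves with LDL response has a smaller SD, the result scales directly. At 8 ng/dL the p = 0.5 row halves to 1.3, 3.8 and 6.4.

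**LDL timing.** LDL is drawn about 5 days before Visit 2, and aldosterone is measured at Visit 2, on the assigned starting dose in both cases. That pair is aligned. Week-12 aldosterone has no aligned LDL value that the text names.

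**The case against.** The article names the dose-relationship as a topic and fixes no method; the analysis plan, which is not shown, might use within-person change or call it exploratory. That is fair as to method. But no analysis plan can create a randomised dose contrast that the design lacks. A within-person change among doubled participants alone mixes the doubling with six more weeks on drug. Comparing them with placebo participants who meet the same LDL criterion sets a selected group of statin takers against what would be nearly the whole placebo arm.

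The magnitude rests on assumptions. The article's own thesis is an effect apart from LDL, so a low correlation is plausible. At 0.1 the false difference is 2.6 ng/dL, and even about 8 is only around 1.2 to 1.4 standard errors. This stands: the table shows what could happen and is no forecast.

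A reader might go further and infer any of the following, which the document does not support:

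- **That all three secondary questions are read at week 12.** No time point is given. The statin-type contrast is also anticipated after two doses and at week 6, both before any doubling.
- **That the week-12 simvastatin-pravastatin comparison is biased.** It remains randomised, and is a valid comparison of two LDL-guided regimens. What it does not give is a comparison at set doses.
- **That the LDL analysis is already mismatched.** The mismatch arises only if week-6 LDL is paired with week-12 aldosterone, which is nowhere stated. A week-12 lipid draw is not listed, but the instruction to repeat the Visit 2 procedures does not clearly exclude one.

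**Conclusion.** The concern holds for the dose-relationship. As designed, the trial cannot deliver that endpoint from a comparison of dose levels: dose within a drug is set by LDL response, and adjustment cannot undo it. With zero true dose effect the false difference is about 2.6 to 13 ng/dL for 30-70% doubled, SD 16 ng/dL and correlations from 0.1 to 0.5, which is roughly 19% to 94% of the 14 ng/dL planning effect. The correlation and the share doubled are assumed, and a smaller response SD lowers these figures in proportion. Confounding follows from the dose rule itself; its size and its direction do not.

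For the LDL relationship the point is narrower: the time point should be fixed, and only week 6 has aligned measurements that the text names. For statin type, the week-12 result needs the right description; it does not need replacing. Separately from titration, one drug per class cannot isolate lipophilicity, so the conclusion foreseen in the Abstract reaches too far. The primary active-versus-placebo test and the sample size are unaffected.

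**What to change.** Leave the titration rule as it is and change the analysis wording:

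1. Do not estimate the dose-relationship by comparing doubled with undoubled participants. Compare the week-6 to week-12 change in aldosterone between whole randomised arms (drug-by-visit interaction against placebo). Read it as the effect of the escalation policy plus further time on drug. Label any doubled-versus-undoubled summary descriptive and non-randomised.
2. Fix the LDL-aldosterone analysis at week 6. Use week 12 only if LDL is also measured then, and state whether it is.
3. Report the week-6 simvastatin-pravastatin contrast as the fixed-dose comparison alongside week 12, and describe week 12 as a comparison of LDL-guided regimens. Give the share doubled in each arm.
4. Limit the Abstract's conclusion to simvastatin versus pravastatin.

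The cost is a little more analysis and a more modest dose-response claim. Items 1, 3 and 4 use data already planned. Item 2 needs a week-12 lipid panel only if the LDL question is to be answered at that time. The sample size does not change.

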**Methods/design:**

One hundred five healthy participants will be recruited from the general population to enroll in a 12-week, randomized, placebo-controlled, double-blinded, 3-arm clinical trial. Ninety participants are anticipated to complete the protocol. After baseline assessment of aldosterone levels, participants will be randomized to daily simvastatin, pravastatin, or placebo. Aldosterone levels will be assessed after 2 days on study drug and again after 6 weeks and 12 weeks on study drug. Prior to each aldosterone assessment, participants will consume an isocaloric sodium and potassium-controlled run-in diet for 5 days. Assessments will occur on an inpatient research unit to control for diurnal, fasting, and posture conditions. The primary outcome will compare 12-week angiotensin II-stimulated serum aldosterone by study drug. Secondary outcomes will compare baseline and 12-week 24-h urine aldosterone by study drug.

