**Fig. 2 Fig2:**
[figure not shown]
Study schema. Participants will be enrolled in the study after completing screening visits. At Study Visit 1, aldosterone levels before and after angiotensin II stimulation will be assessed at baseline before participants are randomized to either simvastatin 20 mg, pravastatin 40 mg, or placebo. Aldosterone secretion will then be assessed 1 day after initiation of study drug in order to determine the acute effects of statin use. Aldosterone secretion will be assessed after 6 weeks at Study Visit 2 and after 12 weeks at Study Visit 3 in order to determine the chronic effects of statin use. Approximately 5 days before Study Visit 2, participants will have their lipid levels checked. If their LDL-cholesterol has decreased by less than 35% since screening, study drug dose will be doubled for the final 6 weeks of the study starting after Study Visit 2. A 5-day low-sodium diet will precede each study assessment. The primary endpoint is comparison of 12-week angiotensin II-stimulated aldosterone secretion between the simvastatin and placebo groups

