To explore the relationship between lipophilicity and effect on aldosterone secretion, we have included two active drug comparator arms in addition to a placebo arm. Our statistical design enables comparison of both drugs independently against placebo, but also affords the ability to gauge across-statin drug impact on aldosterone reduction. In order to maximize the effect of statins to lower aldosterone, we included an intermediate 6-week assessment followed by a study drug dose escalation based on LDL-lowering. If the 6-week LDL-cholesterol level is not reduced by at least 35% from baseline, then the dose of study drug is doubled, allowing an additional 6 weeks at a higher dose in those individuals before final assessment at week 12.

There are several limitations in the study design which may impact the final results. These include standard risks related to study recruitment, retention, and adherence. As mentioned previously, these risks are greatly mitigated by the study design and decades of experience with similar trials. Several assumptions could also influence the study outcome. As opposed to the observational reports in hypertensive and diabetic populations, we chose to study a relatively healthy population in order to reduce confounding and complexity. Therefore, the study population may represent a demographic for whom CV risk, and therefore aldosterone production, is not an immediate concern. However, we strongly believe that these results will be generalizable to disease state populations, and also that aldosterone production in healthy individuals is pertinent due to the chronic nature of CVD and the accumulation of its risk factors over a lifetime. We have attempted to overcome this limitation by instituting several measures to enhance signal detection for aldosterone and reduce environmental noise. Our primary outcome is based on the change in aldosterone levels in response to angiotensin II infusion across study arms. However, this study design includes evaluation after 1 day and 6 weeks on a statin, in addition to the 12-week time-point at which the primary endpoints are evaluated. These additional time-points will lend a preliminary understanding of the time frame by which statins influence aldosterone secretion - namely, whether the effect can be seen acutely after 1 day and/or after 12-week statin treatment.

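### The primary 12-week comparison is sized without baseline and described without adjustment for pre-drug stimulated aldosterone or sex; ANCOVA on data already collected would be more precise

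*Protocol article*

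**What the plan says.** - **Primary comparison.** Abstract, Methods/design: "The primary outcome will compare 12-week angiotensin II-stimulated serum aldosterone by study drug". The Fig. 2 legend narrows this to one pair of arms: "The primary endpoint is comparison of 12-week angiotensin II-stimulated aldosterone secretion between the simvastatin and placebo groups".
- **Different wording in the Discussion.** There the text reads "Our primary outcome is based on the change in aldosterone levels in response to angiotensin II infusion across study arms". This could mean the stimulated level or the within-visit rise from the pre-infusion sample.
- **Sizing.** The Statistical analysis section uses an SD of 16 ng/dL, a difference of 14 ng/dL and 30 per arm, and seeks to "reject the null hypothesis that the aldosterone levels across arms is equal with probability (power) 0.85". On alpha it says "The Type 1 error probability associated with this test is 0.025, since 2 study drugs will be compared independently with placebo".
- **Baseline measurement.** At Study Visit 1, Day 2, aldosterone is measured before and during the same graded infusion, before the first dose. Study Visits 2 and 3 repeat that procedure after the same 5-day diet.
- **Stated use of baseline.** In the Statistical analysis section the arms are "compared for baseline characteristics to assess quality of randomization assignment based on age, BMI, sex, race, and aldosterone levels". No other use of baseline stimulated aldosterone is stated for the primary comparison.
- **Sex.** Randomisation is done "using a block randomization schedule with block size of 3 and maintaining equal distribution of female/male sex".
- **Secondary outcome.** "Secondary outcomes will compare baseline and 12-week 24-h urine aldosterone by study drug". Baseline is mentioned here, but how it enters is not said.

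**The concern.** When an outcome is measured in the same way before and after treatment, the baseline value usually predicts the follow-up value. A comparison of 12-week means that does not use it leaves the whole between-person spread in the error term. Comparing arms at baseline does not replace adjustment. In properly randomised arms any difference is due to chance, and seeing it in a table does not remove it from the estimate.

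What is at stake is the width of the interval and the power if the true effect falls short of 14 ng/dL. That figure comes from observational differences between statin users and non-users, in cohorts that the Discussion describes as hypertensive and diabetic. This trial enrols healthy volunteers, and the Discussion lists the difference as a limitation. The article presents the controlled diet, posture and infusion as ways to sharpen signal detection, and baseline adjustment would use those measurements to the same end.

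**Working it through.** **Inputs from the Statistical analysis section:** difference 14 ng/dL, SD 16 ng/dL, alpha 0.025 per comparison with placebo (sidedness not stated), power 0.85, 30 per arm. **Assumed:** the baseline to 12-week correlation ρ, which the article does not give, taken as 0.3, 0.5 and 0.7; the same SD of 16 at baseline and at week 12; no contribution from sex, because no sex effect on aldosterone is given.

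**Step 1: reproduce the stated sample size with no baseline term.**
SE of the difference = 16 × √(2/30) = 4.13 ng/dL. Noncentrality = 14/4.13 = 3.39. With 58 degrees of freedom and two-sided alpha 0.025 the critical value is 2.30, and the noncentral t power is 0.858. The smallest n per arm that reaches 0.85 is 30, as stated. One-sided 0.025 and two-sided 0.05 each give 25, so they do not match. The stated figure is therefore that of an unadjusted two-sample test on the full SD.

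**Step 2: the same calculation with baseline adjustment.**
Residual SD = 16 × √(1 − ρ²). Degrees of freedom = 58 − 2 = 56 (baseline and sex). Equivalent unadjusted n per arm = 30/(1 − ρ²).

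| ρ (assumed) | Residual SD, ng/dL | SE of difference, ng/dL | Power at 14 ng/dL | Power at 10 ng/dL | Equivalent n per arm |
|---|---|---|---|---|---|
| unadjusted | 16.0 | 4.13 | 0.858 | 0.55 | 30 |
| 0.3 | 15.3 | 3.94 | 0.89 | 0.59 | 33 |
| 0.5 | 13.9 | 3.58 | 0.94 | 0.69 | 40 |
| 0.7 | 11.4 | 2.95 | 0.99 | 0.86 | 59 |

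The 10 ng/dL column is an illustration of a smaller effect, not a figure from the article.

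**Step 3: how much of a chance baseline imbalance reaches the unadjusted estimate.**
The SE of a baseline difference between two arms is also 16 × √(2/30) = 4.13 ng/dL. With equal SDs at both times, a baseline difference d shifts the expected 12-week difference by ρ × d. For a one-SE imbalance:
- ρ = 0.3: 0.3 × 4.13 = 1.2 ng/dL (9% of 14)
- ρ = 0.5: 0.5 × 4.13 = 2.1 ng/dL (15% of 14)
- ρ = 0.7: 0.7 × 4.13 = 2.9 ng/dL (21% of 14)

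**Step 4: sex.** No gain can be computed. If sex is prognostic, leaving out a factor that was balanced at randomisation generally makes the standard error too large, so the error is on the conservative side.

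**The case against.** The strongest objection is that the article names no test, model or covariate list, and nowhere says that the analysis is unadjusted. Its wording of the primary comparison fits an ANCOVA as well as a t-test. Sizing on the unadjusted SD is conservative and commits nobody to an unadjusted analysis. An analysis plan that is not shown may already specify the covariates.

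Much of this stands. A reader might infer that the trial has decided to use the 12-week value alone and to discard its baseline. The documents do not support that: no passage excludes covariates, and baseline is mentioned in the urine aldosterone outcome. Three other tempting readings also fail:
- That a baseline imbalance passes in full into the result, so that one SE would be 30% of the target difference (4.13/14). This would need ρ = 1. The carry-over is ρ times the imbalance, and the unadjusted standard error already allows for it, so it is not an added bias.
- That the article plans significance tests of baseline differences. It speaks only of comparing arms and mentions no test.
- That the urine outcome is not a between-arm comparison. The article says that it is made by study drug.

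The Discussion's wording also leaves open whether the outcome is the stimulated level or the response to the infusion, and the matching covariate depends on the answer.

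The objection does not remove the core. The article does more than stay silent: it states the primary comparison, sizes it without baseline, and gives baseline aldosterone one stated task, which is a check on randomisation.

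**Conclusion.** The point holds as one of efficiency and prespecification, not of error. The stated 30 per arm is correct for its own inputs, and an unadjusted comparison of the randomised arms would be valid. As described, however, the primary comparison is less precise than the collected data allow.

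The size depends on a correlation that the article does not give. At ρ = 0.3 the gain is small (power 0.858 to 0.89); at 0.7 it is worth almost a doubling of the arms (30 to 59). It matters most if the true difference is below 14 ng/dL. These figures assume equal SDs at both visits and that the SD of 16 ng/dL applies to the outcome finally chosen; a within-visit rise could have a different SD and correlation. The case for including sex rests on matching the analysis to the randomisation, not on a computed gain.

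**What to change.** 1. State whether the primary outcome is the stimulated aldosterone level at Visit 3 or the response to the infusion at that visit, and use one wording throughout.
2. Estimate the primary active-versus-placebo contrasts by ANCOVA of that outcome, adjusted for the same measure at Visit 1 Day 2 before the first dose, and for sex.
3. Use the same form for 24-h urine aldosterone: the 12-week value compared between arms, adjusted for its own baseline and for sex.
4. Keep the comparison of arms at baseline as a descriptive table.

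If an analysis plan already says this, the protocol text need only be brought into line with it. The sample size can stay as it is. The cost is a change of wording and about two degrees of freedom, with no new data and no further participants. The choice should be fixed before unblinding, so that level, change and adjusted analyses are not chosen among after the results are seen.
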